**Figure 1. f1:**
[figure not shown]
Study design and follow-up schedule for the CABMILK study. Schematic overview of the CABMILK observational pharmacokinetic cohort study. Lactating mother–infant pairs are enrolled into one of three groups based on their HIV pre-exposure prophylaxis (PrEP) choice: injectable cabotegravir (CAB-LA), oral PrEP (tenofovir disoproxil fumarate/emtricitabine), or no PrEP. The diagram illustrates the expected number per group, timing of PK samples in group A, alongside clinical follow-up visits for safety, growth, and developmental assessments over the eight months follow up.

In the CABMILK Study, three groups of mother-infant pairs will be included as follows: i) 25 mother-infant pairs from a group of lactating mothers who opt to receive long-acting CAB injectable ii) 25 mother-infant pairs from a group of lactating mothers who opt to receive standard oral PrEP comprising tenofovir disoproxil fumarate and emtricitabine, and iii) 50 mother-infant pairs from a group of lactating mothers who chose not to be on oral or injectable PrEP (PrEP unexposed group) (
Figure 1). While this study leverages data collection platforms established by PathToScale and LINK for efficiency, the CABMILK Study independently focuses on evaluating cabotegravir transfer into breast milk and its association with infant safety. The research questions and analyses have been designed to address gaps not explored in the parent studies, ensuring originality and relevance to the local context.

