### Sample size determination and power calculation

Sample size calculation has been primarily based on step 1 of the CABMILK study. Step 2 leverages on the previous step. In Step 1 (Cabotegravir maternal, breastmilk and infant pharmacokinetic study), previous data on 600 mg intramuscular CAB in adults yielded an area under the concentration-time curve (AUC0-∞, μg*h/mL, [range]) of 4172 [2839–6597] with a coefficient of variation of 24%.
^17^ Assuming a similar coefficient of variation, the inclusion of 25 breastfeeding infants will provide >95% precision to estimate overall infant CAB exposure.

Step 2 (Prospective observational cohort follow-up of mother–infant pairs): Detecting rare safety outcomes or subtle neurodevelopmental effects related to cabotegravir exposure would require substantially larger and longer-term studies. Accordingly, Step 2 is designed as a prospective observational cohort to describe infant exposure and characterise safety signals rather than to support formal inferential comparisons. Safety outcomes will include reported adverse events, growth patterns, and changes in developmental status over time.

We plan to enrol 100 mother–infant pairs (25 CAB-LA, 25 oral TDF/FTC PrEP, and 50 PrEP-naïve). This sample size is intended to provide a reasonable descriptive profile of safety and developmental outcomes across exposure groups. The larger PrEP-naïve group will support more stable estimation of background patterns against which findings in the exposed groups can be contextualised.

Child development will be assessed using the CREDI Short Form, a caregiver-reported tool that provides a summary developmental status score suitable for population-level description rather than clinical diagnosis. Assessments over 8 months of follow-up will allow characterisation of short-term developmental trajectories, while recognising that longer-term outcomes cannot be determined within this study.

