### Data analysis

Data will be analysed using either STATA or R.
Table 2 outlines the planned data analyses stratified by the specific objectives of the study. Infant age at every sampling occasion and at every safety and developmental assessment will be recorded to the day. Both postnatal age (PNA) and postmenstrual age (PMA = gestational age at birth + PNA) will be derived for each timepoint and treated as time-varying variables. The population pharmacokinetic model (NONMEM/Monolix) will incorporate, as fixed structural features, allometric size scaling (exponent 0.75 on apparent clearance, 1 on volume of distribution) and a sigmoidal maturation function on apparent clearance, with PMA50 and the Hill coefficient set to published values for UGT1A1 ontogeny rather than estimated from this small cohort. Residual covariate effects of PNA, weight, sex, and feeding pattern will then be tested empirically. To probe the robustness of the maturation assumption, we will conduct a pre-specified sensitivity analysis re-fitting the model with at least one alternative published UGT1A1 ontogeny parameter set (1) and report the resulting impact on individual exposure estimates. Relative infant dose (RID) will be reported overall and by infant-age stratum (<9 months and 9–<12 months). Comparative growth and developmental analyses will use WHO z-scores and age-adjusted CREDI scores; longitudinal mixed-effects models will include infant age at measurement as a continuous covariate. Because exposure groups are self-selected, all comparative analyses are observational and exploratory. Primary safety results will be descriptive: counts, proportions with exact 95% confidence intervals, incidence rates, and Kaplan–Meier curves, without group-comparison p-values. Longitudinal growth and CREDI outcomes will be analysed with mixed-effects models adjusting for a minimal pre-specified set of covariates: infant age at measurement, infant sex, and site. Formal between-group inference for safety is deferred to other larger PK studies. Where feasible, we will perform sensitivity analyses to reduce imbalance, recognising limitations due to our sample size.

**Table 2. T2:** Planned data analyses aligned with study objectives in the CABMILK study.

Objective	Data analysis	Outcome

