To profile the extent of CAB transfer in breast milk and determine its pharmacokinetics in infants whose mothers receive long-acting injectable cabotegravir for HIV preexposure prophylaxis (PrEP).	We will use non-linear mixed effects models to determine the compartmental pharmacokinetics of CAB from maternal plasma to breast milk to infant plasma. We will first calculate the milk: plasma ratio to determine the average milk CAB concentration compared with the average maternal plasma concentration. Second, we will utilise individual predicted infant CAB concentrations to calculate infant overall exposure (AUC0-∞) and estimate CAB infant half-life as well as elimination rate constant. Third, we will estimate the CAB dose ingested by each infant, through breast milk, relative to the maternal dose; the relative infant dose (RID). ^ 25 ^ This RID will allow us to determine the extent of CAB breast milk exposure that would result in attained concentrations in the infant’s blood that are above or below the protein-adjusted IC90 of 0.166 μg/mL. ^ 26 ^	CAB transfer to the infant through breast milk, and profile the attained infant concentrations.
To determine the association of breast milk CAB exposure and infant safety outcomes (growth pattern, neuro-cognitive development, and incidence of adverse events).	Firstly, mean anthropometric indices (weight-for-height, height-for-age, head circumference-for-age) will be compared across three groups using independent t-tests. Secondly, adverse events (overall morbidity) by the end of follow-up will be compared across the three groups using Chi-squared tests. Age-standardised CREDI summary scores (z-scores) analysed as continuous outcomes, reported as adjusted mean differences with 95% confidence intervalsUsing linear regression, we will assess whether breast milk CAB concentrations predict growth patterns and morbidity, adjusting for infant age, sex socio-economic status, birth weight and gestation age at birth. Random effects models will account for intra- and interindividual variability in repeated measurements. Exploring this analysis may inform algorithms for monitoring CAB safety signals in infants. These algorithms could be validated in larger studies and incorporated into routine practice for early detection of CAB-related risks in infants.	Impact of CAB breast milk exposure on infant growth and neurocognitive development in comparison to the standard daily oral PrEP.

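### Table 2 fixes linear regression for the link between milk cabotegravir and infant morbidity, although morbidity is an adverse-event count or an any/none outcome

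*Protocol article*

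**What the plan says.** The second row of Table 2 (Data analysis) gives one model type to two outcomes: "linear regression, we will assess whether breast milk CAB concentrations predict growth patterns and morbidity". The model also carries five adjusters: the infant's age and sex, socio-economic status, weight at birth and gestational age. With the concentration itself, that is at least six slopes.

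The same cell shows what morbidity means: "adverse events (overall morbidity) by the end of follow-up will be compared across the three groups using Chi-squared tests". The text above the table puts safety on the same footing: "Primary safety results will be descriptive: counts, proportions with exact 95% confidence intervals, incidence rates, and Kaplan–Meier curves".

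The cell adds that "Random effects models will account for intra- and interindividual variability in repeated measurements". That sentence deals with repeated measures and names no distribution or link for morbidity. Under Sample size determination and power calculation, generalised estimating equations are offered as an alternative, but for the longitudinal growth indices.

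Only the CAB-LA group can have a milk concentration: "25 mother-infant pairs from a group of lactating mothers who opt to receive long-acting CAB injectable".

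**The concern.** Weight-for-height, height-for-age and head-circumference z-scores are continuous, and a straight line with constant variance is a reasonable model for them. An adverse-event tally is not of that kind. The variance of a count rises with its mean, so if illness does increase with exposure, the scatter is widest where the mean is highest and the usual standard error of the slope is too small. An any/none outcome is bounded by 0 and 1, and a straight line is not.

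This is the only analysis named in the article that relates drug exposure to infant illness within the CAB-LA group. The article says results will stress effect sizes and confidence intervals, so the interval is what readers will use. Table 2 and the dissemination section also say the work may feed algorithms for detecting safety signals. Predicted risks below 0 or above 1 would be awkward there.

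**Working it through.** **No plan figure to reproduce.** The article gives no event rate, effect size or power for this analysis. The 24% coefficient of variation and the precision statement in the sample-size section concern pharmacokinetic exposure and are not inputs here.

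**Inputs from the article.** 25 infants with a milk concentration; five adjusters plus the concentration; milk sampled at month 7 only (before the fifth dose and about 7 days after it; Table 1 and Step 1); exit at month 8.

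**Assumed inputs.** Mean of 1 to 3 episodes per infant over 8 months; overdispersion 0.3; rate ratio (RR) of 1 to 2 per SD of log milk concentration; any/none risk of 0.1 to 0.8.

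**Step 1: who is in the regression.** An infant who leaves before month 7 has no milk concentration and drops out of the model. Those who remain have between 7 and 8 months at risk. The largest shortfall is 1 - 7/8 = 12.5%, so follow-up is close to equal.

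**Step 2: counts.** The model is E(y) = m × exp(βx) × T/8, where x is the standardised log concentration, β = ln(RR), T is between 7 and 8 months for infants who leave early, and y is overdispersed Poisson. Each data set was fitted by ordinary least squares (interval for the best linear slope) and by quasi-Poisson with offset ln(T) (interval for β).

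| True RR per SD | Linear regression, coverage of 95% CI |
|---|---|
| 1 to 1.25 | 94-96% |
| 1.5 | 89-93% |
| 2 | 79-84% |

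Over these scenarios quasi-Poisson covers 92-97%. The linear slope averages 0.96-1.04 of its true value, so it is not materially biased.

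**Step 3: counts with all six slopes.** In a separate simulation with mean counts of 0.5 to 2 and 8,000 data sets per scenario, coverage is about 95% with no association. It is 91.8% and 92.6% at β = 0.5 (RR = exp(0.5) = 1.65) and 86.7% at β = 0.7 (RR = exp(0.7) = 2.01). At least one negative fitted count appears in 7% to 90% of data sets, depending on the scenario.

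**Step 4: any/none with all six slopes.** Coverage is about 95% with no association and 93-96% at a log odds ratio of 1 per SD. At least one fitted risk lies outside 0-1 in 67% to 99% of data sets. The share of all fitted risks outside the range is 6% at a true risk of 0.5 and 25% at 0.1, both with no association.

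**Step 5: number of covariates.** Events per slope = 25 × risk / 6. At risks of 0.1, 0.3 and 0.5 this is 0.4, 1.25 and 2.1. Ordinary logistic regression with the full covariate list would be unstable, so changing the model family alone is not enough.

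**The case against.** The strongest reply is that little harm follows. The analysis is exploratory. The main safety results are already planned as counts, exact proportions, incidence rates and Kaplan-Meier curves, which suit event data. A linear model for any/none data estimates a risk difference, and its interval covers close to nominally. The plan reports effects and intervals, not individual predicted risks.

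The effects at which coverage fails may also be large. If milk concentration varied like the adult plasma exposure in the sample-size section (CV 24%, an assumption for milk), the SD of log concentration would be √ln(1 + 0.24²) = 0.237. An RR of 1.5 to 2 per SD would then mean 1.5^(0.693/0.237) = 3.3 to 2^(0.693/0.237) = 7.6 per doubling. At CV 50% the SD is 0.472 and the range is 1.8 to 2.8 per doubling. Finally, a separate statistical analysis plan is cited under Data Availability and may define morbidity and its model.

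Most of this stands and sets the severity. It does not remove the point. Table 2 does not leave the model open; it names one that does not fit the outcome as described beside it. The descriptive safety summaries do not model concentration. The intervals fail when exposure strongly affects illness, which is the case a safety-signal analysis exists to find.

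A reader might also infer that infants who leave early look healthier and that the slope is therefore biased towards zero. The documents do not support this: milk is sampled only at month 7 of 8, so early leavers are not in the regression, and the slope is close to unbiased among those who are.

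**Conclusion.** The mismatch is real and minor. Table 2 fixes linear regression for an outcome that the article elsewhere treats as any/none, a count or a rate, and nothing else in the article corrects this.

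Its size depends on how morbidity is defined and on how strong the association is. Interval error is essentially confined to counts with a strong association, and a count model largely avoids it there. For any/none morbidity the defect is implausible fitted risks, not poor coverage. These figures rest on assumed event rates, overdispersion and effects, because the article gives none.

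Two wider conclusions would go too far. The intervals are not wrong in general, since they are about right with no or a modest association. The primary pharmacokinetic objective is not touched.

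**What to change.** In Table 2, second objective:

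- Define morbidity for this analysis, either as the number of episodes per infant or as any/none.
- Keep linear (mixed) models for growth z-scores only.
- For episode counts, use quasi-Poisson or negative binomial regression with log person-time as offset. The offset will have little effect here, but it is the correct form.
- If morbidity is any/none, use Firth-penalised logistic regression.
- Reduce the covariate set for morbidity, given 25 infants.
- Report rate ratios or odds ratios with 95% confidence intervals, labelled exploratory.

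The cost is a sentence or two in Table 2 and matching text in the statistical analysis plan. No new data or participants are needed, and because enrolment is still under way the change can be made before analysis.

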**Figure 2. f2:**
[figure not shown]
Pharmacokinetic sampling schedule for the CABMILK study. Timeline of maternal plasma, breastmilk, and infant dried blood spot (DBS) sample collection used to characterize cabotegravir pharmacokinetics and infant exposure during breastfeeding. The sparse PK sampling visit occurs at month 7 after enrolment, corresponding to the fifth CAB-LA injection, after participants have received four prior injections. This schedule enables estimation of maternal drug concentrations, milk-to-plasma ratios, and infant exposure metrics.

**Table 1. T1:** Schedule of study procedures and sample collection in the CABMILK study.

Visit description											
Visit number	1	2	3	4	5	6	7	8	9	10	Unscheduled
Visit month	0	1	3	5	7	7	7	7	7	8	Any
Visit study time	Pre- dose	Pre- dose	Pre- dose	Pre- dose	Pre-dose (0 hr)	24 hr	Day 7±3	Day 14±3	Day 28±5	Study exit	Sick visit
Screening and enrolment											
Informed consent discussion	x										
Medical and drug history	x										x
Revision of eligibility criteria	x										
ID number assignment	x										
Capillary haemoglobin measurement	x				x						
Group A: Mother-infant pairs on cabotegravir PrEP											
General physical examination	x	x	x	x	x	x	x	x	x	x	x
Recording of current and concomitant medication	x	x	x	x	x	x	x	x	x	x	x
Anthropometric measurements to assess growth ^#^	x	x	x	x	x					x	
Cognitive and neuro-assessment using a validated tool such as MDAT or equivalent	x	x	x	x	x					x	
Adverse events assessment	x	x	x	x	x	x	x	x	x	x	
Maternal venous blood PK sample					x		x				
Mandated breastmilk feeding or record of latest time of feeding*							x				
Maternal breastmilk PK sample					x		x				
Infant capillary blood PK sample					x	x	x	x	x		
Infant feeding patterns and record of any food supplementation	x	x	x	x	x	x	x	x	x	x	x
Groups B & C: Mother-infant pairs in oral PrEP group and PrEP naïve											
General physical examination	x	x	x	x	x					x	x
Recording of current and concomitant medication	x	x	x	x	x					x	x
Anthropometric measurements to assess growth ^#^	x	x	x	x	x					x	
Cognitive and neuro-assessment	x	x	x	x	x					x	
Adverse events assessment	x	x	x	x	x					x	

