### Step 1-
CABMILK study- Cabotegravir maternal, breastmilk and infant pharmacokinetic study

We hypothesise that cabotegravir administered as long-acting PrEP in lactating mothers may be detectable in breast milk and infant plasma, but that the magnitude of infant exposure and its clinical significance remain uncertain. The study is designed to quantify breast milk transfer, estimate infant systemic exposure, and evaluate infant safety. If infant exposure occurs at very low, subtherapeutic concentrations, this could have theoretical implications for resistance in the event of HIV acquisition during breastfeeding; however, it is also possible that transfer is minimal and clinically reassuring and safe. CAB would transfer.

*Cabotegravir pharmacokinetic sampling: maternal plasma, breastmilk, and infant plasma*

25 lactating mothers initiating CAB PrEP within the PathToScale Study or LINK Study will be approached for participation in the study. Since CAB has a half-life of 40 days
^
9,
14
^ it would be expected to attain a steady state in the mother at least after 4 half-lives
^
16
^ (i.e. in the case of CAB, at least 160 days) from the first initial dose. To ensure that we conduct pharmacokinetic sampling of CAB at steady state, we will collect samples for CAB concentrations before the 5th CAB maternal dose (i.e. before the maternal dose at 7 months postpartum).

In mothers, 5 mL of venous blood will be collected using calibrated EDTA tubes. It will be separated in the laboratory to collect plasma and frozen in at least two aliquots at -80 degrees Celsius in readiness for a validated liquid chromatography–tandem mass spectrometry (LC–MS/MS) assay. Breastmilk CAB samples will be paired and collected by manual expression at pre-dose and at the expected time of maternal peak (Cmax), 7 days (±3) post-5th CAB dose. No more than 5 mL of breast milk will be collected in a clear container at each sampling time point. Thereafter, the sample will be frozen in at least two aliquots and stored at -80 degrees Celsius in readiness for cabotegravir assay. Therefore, each mother will contribute two breastmilk and blood samples.

To characterise and profile infant CAB exposure from breastmilk, 200 μL of infant capillary blood will be collected through a finger/heel prick at the expected time of trough- (sample collected before dosing in the mother) and peak (expected Cmax) concentrations at 7 days (±3)
^
17

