### Step 2-
Cabotegravir safety, growth pattern and development study

We hypothesise that there will be no difference in the incidence of adverse events or illnesses, growth, and development between infants exposed to breast milk CAB and those exposed to breast milk oral PrEP. 25 mother-infant pairs from Step 1 (mothers receiving CAB for PrEP), 25 other mother-infant pairs from the oral PrEP group of the PathToScale and LINK studies and 50 mother-infant pairs naïve of PrEP, matched to those in the CAB PrEP group, will be followed up for eight months from the time of maternal PrEP initiation in the PrEP groups or a similar time in the PrEP naïve group. The PathToScale and LINK studies are following up mothers in the CAB group from the initiation visit, 1 month later and, thereafter, every 2 months. In our study we will follow a similar schedule for all three groups with a final exit visit scheduled at eight months post initial CAB dose. This will result in 10 scheduled visits in the CAB group and six in the oral PrEP and no PrEP groups. The CAB LA PrEP group will have four additional visits for PK sampling at month 7. In the present CABMILK Study, we will utilise all six planned visits to assess the incidence of reported adverse events and infant growth by measuring anthropometric indices (weight-for-height and height-for-age) as well as head circumference-for-age. The same visit schedule and safety assessments will be applied to the oral PrEP and PrEP-naïve groups. Infant growth and neurodevelopment will be longitudinally assessed at all six study visits using the Caregiver Reported Early Development Instrument (CREDI).

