To support policy and programmatic decision-making, tailored briefs and technical summaries will be provided to the Malawi Ministry of Health, the NHSRC, and other national stakeholders. The results will be presented in multisectoral learning sessions to inform national CAB-LA rollout and strengthen maternal–child health pharmacovigilance. A key output will be early algorithms for detecting potential safety concerns in infants exposed to cabotegravir through breast milk, with the aim of integrating these into routine monitoring systems.

Public dissemination will prioritise accessibility and clarity. Lay summaries, infographics, and materials in English and Chichewa will be shared through health facility posters and digital platforms such as social media and WhatsApp. Engagement with community advisory boards and mother support groups will ensure that the findings are understood and can inform community dialogue.

Data sharing will follow open science principles, while protecting participants’ confidentiality. Aggregated datasets, breastmilk pharmacokinetic summaries, and analysis codes will be shared on Wellcome Open Research and an MLW-managed repository. De-identified individual-level data will be available upon reasonable request under a governed access model. Protocols, analysis plans, and metadata will be openly accessible to support reproducibility and wider scientific use.

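### Growth and morbidity are to be predicted from milk concentrations that are first measured at month 7 of 8, and morbidity is put into a linear regression

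*Protocol article*

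**What the plan says.** The infant-safety row of Table 2 (Data analysis) states that, by linear regression, "we will assess whether breast milk CAB concentrations predict growth patterns and morbidity". The adjustment set is infant age, sex, socio-economic status, birth weight and gestational age, and random effects are planned for repeated measurements. The row adds that this work may inform safety-monitoring algorithms.

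Under Step 1, milk is collected at "pre-dose and at the expected time of maternal peak (Cmax), 7 days (±3) post-5th CAB dose", so that "each mother will contribute two breastmilk and blood samples". The Figure 2 legend fixes the study time: "The sparse PK sampling visit occurs at month 7 after enrolment, corresponding to the fifth CAB-LA injection". Table 1 marks breast milk only at visits 5 and 7, both in month 7.

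Under Step 2, "we will utilise all six planned visits to assess the incidence of reported adverse events and infant growth". Follow-up ends with "a final exit visit scheduled at eight months post initial CAB dose".

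The Dissemination and data sharing plan says: "A key output will be early algorithms for detecting potential safety concerns in infants exposed to cabotegravir through breast milk".

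**The concern.** The predictor is first observed when follow-up is nearly over, while most of the outcome data come from earlier visits. A concentration measured at month 7 can explain growth at months 1 to 5 only if it represents the mother's exposure at those times. The article does not say that it does, and it does not say that model-predicted earlier exposure will replace the measured value.

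The row also gives one model type for two kinds of outcome. Growth indices are continuous. Morbidity, which the same row summarises as adverse events over follow-up, is an event or a count.

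At stake is what may be concluded about exposure and infant safety in the cabotegravir group, and how much weight the monitoring algorithms can bear.

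**Working it through.** **Visit counts (Table 1 and Step 2).** Cabotegravir-group visits fall at months 0, 1, 3, 5, 7, 7, 7, 7, 7 and 8, which is 10. The other groups attend at months 0, 1, 3, 5, 7 and 8, which is 6. The difference is 4. This reproduces the article's own 10, 6 and 4 additional PK visits.

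**Outcome visits against the first milk sample (visit 5, month 7, pre-dose).**
- Growth, month 0: pre-dose baseline, so not an outcome of exposure.
- Growth, months 1, 3 and 5: before any milk sample.
- Growth, month 7: same visit as the first milk sample.
- Growth, month 8: after both milk samples.
- Adverse events in the cabotegravir group: four scheduled assessments before (months 0, 1, 3, 5), one at, and five after (visits 6 to 10). All five later ones fall in the last month.

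**Share of follow-up.** Before the first milk sample: 7 / 8 = 87.5%. After the second, taking a month as 30.4 days: (30.4 − 7) / (8 × 30.4) = 23.4 / 243.2 = 9.6%. Over the ±3-day window this runs from 20.4 / 243.2 = 8.4% to 26.4 / 243.2 = 10.9%.

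**Could month 7 stand for earlier exposure?** Step 1 takes a 40-day half-life and at least 160 days to steady state. Month 5 is 5 × 30.4 = 152 days, so by that rule none of the earlier visits is at steady state. A simple check is more favourable. Assume that milk follows plasma, that decline is single-exponential with no absorption phase, and that doses are equal and on time at months 0, 1, 3 and 5. The relative trough at month m is the sum over earlier doses d of exp(−k × (m − d) × 30.4), with k = ln 2 / half-life.

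At 40 days, k = 0.01733:
- Month 1: exp(−0.527) = 0.590.
- Month 7: 0.025 + 0.042 + 0.122 + 0.349 = 0.538.
- Ratio: 0.590 / 0.538 = 1.10.

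| Half-life (days) | Month 1 | Month 3 | Month 5 | Month 7 |
|---|---|---|---|---|
| 30 (assumed) | 1.51 | 1.12 | 1.02 | 1.00 |
| 40 (article) | 1.10 | 1.03 | 1.01 | 1.00 |
| 50 (assumed) | 0.88 | 0.95 | 0.99 | 1.00 |

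With full adherence, troughs from month 3 are fairly flat; month 1 depends on the half-life. Adherence matters more. If the month-3 injection were missed and not made up (illustration, 40 days), the month-5 trough would be 0.072 + 0.122 = 0.193 and the month-7 trough 0.025 + 0.042 + 0.349 = 0.416. The ratio is 0.193 / 0.416 = 0.46, so month 7 would overstate month-5 exposure about twofold. The Missed visits section expects missed doses to occur.

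**Feeding.** Enrolment runs from the first week of life to under 5 months of age. Infants at month 7 are therefore aged roughly 7 to under 12 months (0 + 7 to 5 + 7). A milk concentration at that age carries no information on how much milk was taken earlier.

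**Covariates side by side.**
- Table 2: age, sex, socio-economic status, birth weight, gestational age.
- Data analysis text, for the growth and CREDI mixed models: a minimal set of age, sex and site.
- Inclusion and exclusion criteria: gestational age will serve as a covariate.
- Section on other factors affecting milk exposure: feeding enters the safety analyses as a time-varying covariate.

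Table 2 lacks feeding and site; the minimal set lacks gestational age and feeding.

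**The case against.** The strongest defence is that sampling was deliberately placed at steady state, so a month-7 level is a fair summary of a mother's usual exposure. The check above supports this in part: with on-time dosing and a 40-day half-life, troughs from month 1 on lie within about 10% of month 7. What remains is that the assumption is unstated for this regression and fails where doses are missed or late.

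Feeding is not ignored either. It is recorded at every visit and promised as a time-varying covariate. That stands, and the gap is only that the Table 2 model does not carry it.

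The article calls the comparative work exploratory, says results will be read as observational associations, and discloses that it is not powered for subtle differences. Low power is therefore no part of this point. The exploratory status lowers the consequence, but it does not make the predictor fit the schedule.

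A reader might infer that the exposure is measured wholly after the outcome. The documents do not support that: the month-8 growth visit and the last month's adverse events follow the first milk sample, and the regression's outcome window is not spelled out. The reading that all visits enter rests on the use of all six visits and on the repeated-measures wording. A reader might also infer that the comparison groups enter with zero concentrations. No section says so, and milk is sampled only in the cabotegravir group. CREDI has its own analysis in the same row and is not a named outcome of this regression.

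**Conclusion.** The point holds in a limited form. As written, the regression cannot show that milk concentration predicts growth or morbidity unless month-7 levels represent earlier exposure. Three of five post-baseline growth visits and 87.5% of adverse-event follow-up precede the first milk sample. This rests on Table 1 as printed and on the inference that outcomes from all six visits enter the model. If the outcome were confined to the period after month 7, the order of time would be right, but only one growth visit and about one month of adverse events would remain.

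The model for morbidity is a separate defect and does not depend on the timing argument.

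A reader might conclude that the algorithm output should be abandoned. That goes too far: Table 2 says only that the analysis may inform algorithms to be validated in larger studies. The Dissemination section's stronger wording is what needs toning down.

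**What to change.** - **Exposure.** In the cabotegravir group, treat month 0 as baseline. Relate each later assessment to milk exposure up to that time, predicted by the planned population PK model, and state the steady-state assumption. Alternatively, keep the measured month-7 concentration and report the result only as an association with month-7 exposure.
- **Morbidity.** Use a Poisson or negative-binomial model with follow-up time for counts, or a logistic model for any event.
- **Covariates.** Add the promised time-varying feeding covariate, and reconcile the Table 2 list with the minimal set in the Data analysis text and with the commitment to adjust for gestational age.
- **Wording.** Replace the language of prediction with association, and describe the algorithms in the Dissemination section as hypothesis-generating.

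The cost is text changes and some added modelling, with no new samples. Predicted exposure needs each mother's actual injection dates. The article does not say that these are captured, so their availability from the parent studies should be confirmed. The downside is that predicted exposure before month 7 still rests on the PK model and on month-7 data. It makes the stability assumption explicit but does not remove it.
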